#### Randomization

A cluster randomization at the level of the cooperation units, consisting of a GP practice and one or more community pharmacies, will be performed. Thus, all patients within a GP practice belong to the same group (either intervention or control group). The randomization is stratified by study center (Munich, Bielefeld, Witten), and the intervention and control groups are randomized in a 1:1 ratio. The random allocation sequence will be generated by the Center for Clinical Studies Regensburg by block randomization using SAS (version 9.4; SAS Institute Inc., Cary, NC, USA) and the procedure *proc plan*. Randomization lists will be stored at the Center for Clinical Studies and are concealed from the study centers until the end of the study. Allocation of a cluster to a treatment group will be directly after completion of patient recruitment within the cluster (see Figure 3).

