#### Statistical analysis

A generalized linear mixed model (GLMM) is used for the analysis of the primary binary endpoint (reduction of ⩾0.15 points on the DBI at 6 months follow-up). In this model, the patients are nested under the cooperation units (clusters) with a random intercept for each cluster, whereby the number of degrees of freedom is determined using the between-within method.^
45
^ The GLMM is adjusted for study center and the known prognostic factors age, sex, and type and number of PSA-PIM at time T_0_. ORs with associated 95% confidence intervals are reported as effect sizes. In additional sensitivity analyses, the GLMM is adjusted for other covariates potentially associated with the primary endpoint.^
46
^ Subgroup analyses are planned to identify any differential effects of the intervention on different PSA-PIM drug groups. The study population for the primary analysis is based on the intention-to-treat principle, with a per-protocol analysis performed as a secondary analysis. Secondary endpoints will be presented descriptively and analyzed exploratively using the appropriate methods. All planned statistical analyses (including handling of missing data) will be prespecified in a Statistical Analysis Plan before the end of the study, which will be accessible at the Center for Clinical Studies Regensburg.

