#### Statistical analysis

The health economic evaluation follows a three-step procedure previously recommended for health economic analyses in Germany.^
47
^ Cost analysis employs a *difference-in-differences* (DiD) approach to compare trends in individual healthcare cost estimates between the intervention group and the control group, incorporating both direct and indirect costs.

In the first step, utility analysis is conducted using the DiD method to compare changes across the five utility dimensions at the individual level. Utility differentials are calculated between the four survey periods and subsequently compared between the IG and CG using hypothesis testing. For instance, for a patient *i*, the first differences in some utility index between periods 0 and 1 are

$$\Delta u_{i,1}:=u_{i,1}-u_{i,0},$$

With *μ*_i,0_ being the observation for the respective utility index at *T*_0_ for patient *i*. We check the null hypothesis that the utility differentials are not associated with whether the patients belong to the IG or the CG, that is, for

$$\Delta u_{i,t}=\delta I+\beta \prime x_{i},$$

we check

$$H_{0}:\delta =0.$$

Here, *I* is a binary variable that takes the value 1 for patients of the IG and 0 for those in the CG. **
*x*
**_i_

$x_{i}$
 is a vector of sociodemographic predictors. Those are included to avoid a potential bias in the test results because of heterogeneities between the two study groups. If the null hypothesis of interest can be rejected, the intervention is associated with different utilities than the standard treatment. The Greeks are parameters estimated based on the data via ordinary least squares.

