If the intervention does not lead to a deterioration in health utility, cost analysis will estimate cost differentials between the intervention and control groups using an approach similar to that applied for the utility dimensions. If the initial steps of the analysis do not demonstrate clear dominance of one care alternative over the other (i.e., neither intervention nor control prevails), cost-effectiveness analysis will be conducted, computing an incremental cost-effectiveness ratio (ICER). Analysis is conducted from the perspective of the SHI community, with the time horizon covering at least the study observation period. To address statistical uncertainty, stochastic sensitivity analyses will be performed using Monte Carlo simulations. These simulations generate empirical distributions of the ICER by simulating utility and cost indices 10,000 times. This approach provides an ICER distribution that can be used to estimate the probability of the intervention meeting prespecified cost-effectiveness thresholds, similar to methods described in Gillespie et al.^
48
^

ICERs will be calculated for all five utility dimensions to provide a comprehensive basis for healthcare decision-making. However, given the recognized importance of the EQ-5D index in health economic evaluations, recommendations for implementing the intervention into standard care will be primarily based on its cost-effectiveness analysis. The Monte Carlo simulations generate empirical distributions for both the utility (denominator) and cost (numerator) components of the ICERs based on 10,000 simulations of the overall cost and utilities change associated with the intervention through the observed period *T*_0_–*T*_4_. The nuisance parameters used for this are estimated by the earlier-mentioned regression models. For instance, the ICER in the trajectory *s* is:

$${\mathrm{ICER}}_{s}=\frac{\Delta u_{0-4,s,\mathrm{IG}}-\Delta u_{0-4,s,\mathrm{CG}}}{\Delta c_{0-4,s,\mathrm{IG}}-\Delta c_{0-4,s,\mathrm{CG}}},$$

with

$\Delta \mu_{0–4,s,\mathrm{IG}}$
: average utility differential between *T_0_* and *T_4_* for intervention group in trajectory *s*,
$\Delta \mu_{0–4,s,\mathrm{CG}}$
: average utility differential between *T_0_* and *T_4_* for control group in trajectory *s*,
$Dc_{0–4,s,\mathrm{IG}}$
: average cost differential between *T_0_* and *T_4_* for intervention group in trajectory *s*,
$Dc_{0–4,s,\mathrm{CG}}$

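### The health-economic utility and cost models are patient-level least squares with no cluster term and no study center, so their standard errors and tests do not match a cluster-randomized, center-stratified design; ignored clustering is the larger error.

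*Protocol article*

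**What the plan says.** The Statistical analysis section of the Health economic evaluation sets out a difference-in-differences method to "compare changes across the five utility dimensions at the individual level". Its equation has two terms: the arm indicator, whose coefficient is tested against zero, and a covariate vector x. That vector "is a vector of sociodemographic predictors. Those are included to avoid a potential bias in the test results". The estimator is given as well: "The Greeks are parameters estimated based on the data via ordinary least squares".

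Costs are analysed "using an approach similar to that applied for the utility dimensions". The 10,000-run ICER simulation depends on the same fits: "The nuisance parameters used for this are estimated by the earlier-mentioned regression models".

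The cluster-randomized trial is described differently. Under Randomization, the units allocated are cooperation units of one practice with its pharmacies, and "The randomization is stratified by study center (Munich, Bielefeld, Witten), and the intervention and control groups are randomized in a 1:1 ratio". The primary analysis gives each cluster a random intercept, uses between-within degrees of freedom, and states: "The GLMM is adjusted for study center and the known prognostic factors age, sex, and type and number of PSA-PIM".

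**The concern.** Two features of the design are missing from the economic models: the cluster, which is the unit that was randomized, and the center, within which it was randomized. The same article includes both in its primary model.

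The two omissions push the reported standard error in opposite directions. Treating patients of one practice as independent makes it too small. Leaving a balanced stratification factor in the residual makes it too large. What matters is the net effect under the model as written.

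The stakes are real. The utility result decides how the evaluation proceeds to costs and to the ICER, and the recommendation on routine care is to rest mainly on the cost-effectiveness analysis of the EQ-5D index. Standard errors that are too small produce too many significant utility and cost differences. They also make the ICER distribution too narrow to the extent that the simulation draws on them.

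**Working it through.** **Inputs from the protocol article.** Sample size: ICC 0.05; 6 analysed and 8 recruited patients per cluster; 22 clusters per arm; 10% versus 25% responders; power 80%; alpha 0.05. Randomization: three centers, 1:1.

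**Assumptions.** The test is two-sided. The ICC of utility and cost changes is not given, so 0.05 is borrowed from the primary endpoint and 0.01 to 0.10 is shown as a range. Conventional least-squares standard errors are used, since no other kind is named. Center variance v is not given; 0, 5 and 10% of the within-center patient variance are tried.

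**Step 1: the plan's own figure.** Design effect = 1 + (6 − 1) × 0.05 = 1.25. With a cluster-level t test on 2(k − 1) degrees of freedom, power is 79.7% at k = 21 and 81.6% at k = 22 clusters per arm. That gives 22 × 2 × 6 = 264 analysed patients, and 264 / 0.75 = 352 recruited. The stated figures reproduce, so the sample size does allow for clustering.

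**Step 2: clustering ignored in the economic models.** The true standard error is √DE times the one reported, where DE = 1 + (m − 1) × ICC. The true level is 2 × [1 − Φ(1.96 / √DE)].

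| m | ICC | DE | √DE | true level |
|---|---|---|---|---|
| 6 | 0.01 | 1.05 | 1.025 | 5.6% |
| 6 | 0.05 | 1.25 | 1.118 | 8.0% |
| 6 | 0.10 | 1.50 | 1.225 | 11.0% |
| 8 | 0.01 | 1.07 | 1.034 | 5.8% |
| 8 | 0.05 | 1.35 | 1.162 | 9.2% |
| 8 | 0.10 | 1.70 | 1.304 | 13.3% |

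At ICC 0.05 the reported standard error is too small by 1 − 1/1.118 = 11% (m = 6) to 1 − 1/1.162 = 14% (m = 8).

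**Step 3: center omitted as well.** In patient-level least squares, center variance enters the residual once, so the reported variance is proportional to 1 + v. Stratification has removed center from the true variance, which is proportional to DE. The ratio of reported to true standard error is √[(1 + v)/DE]. For m = 6 it is √(1.05/1.25) = 0.92 at v = 5% and √(1.10/1.25) = 0.94 at v = 10%. Both are below 1. At ICC 0.05, v would have to exceed 25% (m = 6) or 35% (m = 8) before the net error turned conservative.

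**Step 4: simulation.** The settings were 44 clusters of equal size in three centers (16, 14, 14), allocation 1:1 within center, no true effect, ICC 0.05 and 5,000 runs per setting. The Monte Carlo standard error near 5% is √(0.05 × 0.95/5000) = 0.3 percentage points. Type I error at nominal 5%, for v = 0 / 5 / 10%:

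| analysis | m = 6 | m = 8 |
|---|---|---|
| patient-level OLS, no center | 7.9 / 7.7 / 7.1% | 10.0 / 8.8 / 7.7% |
| patient-level OLS with center | 8.0 / 8.5 / 8.7% | 10.1 / 9.8 / 9.4% |
| cluster means, no center | 4.9 / 2.7 / 2.2% | 5.2 / 2.4 / 1.5% |
| cluster means with center | 5.0 / 5.1 / 5.4% | 5.3 / 5.0 / 5.3% |

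Only the analysis that respects both the cluster and the center holds the nominal level throughout. Adding center to least squares leaves the excess in place and, where centers differ, raises it slightly.

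**The case against.** **Condensation.** A journal article need not list every covariate or the type of standard error, and an analysis plan is promised. That is fair for the exact members of x. It does not answer the point, because this section announces a detailed methodological description and then states the equation, the class of covariates and the estimator. What is stated does not fit the design.

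**Differencing.** The outcome is change from baseline, so stable regional differences in service use cancel within the patient, and the unit costs are national. This stands. Only center differences in change over time matter, and the document gives no figure for them. It is one reason why center is the smaller half of the point. Differencing does not remove clustering of the changes, since practices implement the intervention and manage follow-up as units.

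**A stronger reading about center.** A reader might infer that the missing center term is the main fault, that it makes the cost and utility intervals about 2 to 10% too wide, and that it wastes about a sixth of the information. Figures of that kind come from a cluster-level calculation with assumed center variances of 1 to 5%. The protocol describes patient-level least squares, where the net error runs the other way (Step 3).

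**Bias.** A reader might also infer a biased comparison between arms. Allocation is 1:1 within center, and the range of 6 to 15 patients per practice and the 25% allowance for loss apply to both arms. No expected imbalance of center by arm follows.

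**Conclusion.** The point holds as a mismatch between the economic models and the design. Under the least-squares models as written, standard errors are about 11 to 14% too small and the true level is about 8 to 9%, if the ICC of 0.05 carries over and conventional standard errors are used. For ICCs of 0.01 to 0.10 the level is about 5.6 to 13%. Center variation offsets this only slightly at the values tried.

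The center omission has its own, smaller effect. Once clustering is respected, leaving center out makes the test conservative (about 1.5 to 2.7% at nominal 5% for the center variances of 5 and 10% tried) and gives up a little precision. The true extent depends on how far change over time differs by center, which cannot be read from the document.

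The primary analysis is not affected. The effect on the ICER distribution cannot be sized, because the protocol does not say in detail how the simulation draws its uncertainty.

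**What to change.** In the Statistical analysis section of the Health economic evaluation:

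- Add study center to x as two indicators, beside the sociodemographic predictors.
- Replace plain least squares by a model with a cluster random intercept, or keep the coefficients and use cluster-robust standard errors. In either case use small-sample degrees of freedom. With 44 clusters, an intercept, arm and two center indicators, 44 − 4 = 40 between-cluster degrees of freedom remain.
- Apply the same specification to every utility model, every cost model and the models that feed the ICER simulation, so that the simulated uncertainty reflects the clusters.
- Make both changes together. Center alone leaves the test anti-conservative.

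Adding baseline type and number of PSA-PIM, as in the primary model, is optional.

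The cost is a short change of text and somewhat wider reported intervals (by a factor of about 1.12 to 1.16 at an ICC of 0.05). No new data are needed, as cluster and center are known for every patient.

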#### Study design

The trial uses a multicenter, cluster-randomized design with two parallel arms and a 1:1 allocation ratio. The intervention arm receives the PARTNER intervention, while the control arm undergoes enhanced treatment as usual (eTAU). To minimize patient selection bias, clusters are blinded to their treatment allocation and the intervention’s focus on PSA-PIMs until patient recruitment is finalized in each cluster. After randomization, only the intervention arm will be unblinded. The PARTNER intervention includes cluster-level components (outlined below), and a patient-randomized design was deemed unsuitable due to the high risk of contamination in the control arm, making cluster randomization the preferred approach.

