#### Sample size

Sample size calculation is based on the primary endpoint, the proportion of patients with a relevant reduction in DBI of at least 0.15 points at T_2_ (6 months after T_0_) compared to T_0_. Based on a Dutch intervention study^
44
^ and a slight positive effect expected in the control arm, we estimate the proportion of patients with a relevant reduction in DBI in the control arm to be 10%. Based on the successful Canadian EMPOWER study,^
14
^ whose main intervention component (patient empowerment by pharmacists) we adopt in the PARTNER intervention, we expect the proportion of patients with a relevant reduction in DBI to be 25% in the intervention arm. This corresponds to an absolute risk difference of 15% and an odds ratio (OR) of 3. Furthermore, we estimate the intra-cluster correlation coefficient (ICC) to be 0.05 and the average cluster size to be *n* = 6 patients. To be able to show a difference in responder rates of 10% versus 25% with a power of 80% at a significance level *α* = 0.05 with an ICC = 0.05, 22 clusters per group with a total of *n* = 264 patients are required. Under the conservative assumption of a maximum loss-to-follow-up of 25%, 352 patients (8 patients per cluster) will be recruited. Sample size was calculated using R software (version 4.1.1; R Foundation for Statistical Computing, Vienna, Austria).

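### The health-economic regressions are written as patient-level OLS with no allowance for clustering, so fitted as written their standard errors are too small whenever the ICC is positive

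*Protocol article*

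**What the plan says.** All references are to the protocol article.

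- **Design.** Under 'Study design': "The trial uses a multicenter, cluster-randomized design with two parallel arms and a 1:1 allocation ratio". Under 'Randomization', the unit is the cooperation unit of one GP practice and its pharmacies, so all patients of a practice are in the same arm.
- **Sample size.** The calculation assumes an ICC of 0.05 and an average of 6 analysed patients per cluster, for the binary DBI responder endpoint.
- **Primary analysis.** In the GLMM, "the patients are nested under the cooperation units (clusters) with a random intercept for each cluster", with between-within degrees of freedom.
- **Health-economic model.** Under 'Health economic evaluation', 'Statistical analysis', the change in a utility index for patient i is written as δI + β′x_i. I is the arm indicator, and x_i "is a vector of sociodemographic predictors". The null hypothesis is δ = 0, and the estimator is given thus: "The Greeks are parameters estimated based on the data via ordinary least squares".
- **Costs and ICER.** Cost differentials are to be estimated in a similar way. On the 10,000 simulations of the ICER: "The nuisance parameters used for this are estimated by the earlier-mentioned regression models".

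The health economic part contains no cluster effect, no cluster-robust variance and no cluster-level resampling.

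**The concern.** Arm is constant within a cluster. If patients of one practice resemble each other in their change in utility or cost, they carry less information about the arm effect than the same number of independent patients. OLS with its usual standard errors ignores this and understates the variance of δ. The trial allows for clustering in its sample size and primary model, but the economic model as written does not.

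Clustering in costs is plausible from the protocol itself. Direct costs count the time of GPs, nursing staff and pharmacists, and the portal and workshop are delivered to whole clusters.

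These tests steer the economic evaluation. Cost analysis follows if utility does not deteriorate, and an ICER is computed if neither alternative clearly dominates. The simulated ICER distribution then gives the probability of meeting cost-effectiveness thresholds, and the recommendation on standard care rests mainly on the EQ-5D version of that analysis.

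**Working it through.** **Inputs.** From 'Sample size': ICC 0.05 (primary endpoint only), 6 analysed patients per cluster, 22 clusters per group, 264 analysed, 25% loss, 352 recruited (8 per cluster), responder rates 10% and 25%, α 0.05, power 80%. Two-sided testing is assumed. ICC values for change in utility and cost are not given and are assumed below.

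**The plan's own figure.**
- Unclustered n per arm, with mean proportion 0.175: (1.960·√(2·0.175·0.825) + 0.842·√(0.09 + 0.1875))² / 0.15² = 99.5, so 100.
- Design effect: 1 + (6 − 1)·0.05 = 1.25, so 125 per arm, and 125/6 = 20.8 clusters.
- Rounding up gives 21. With t quantiles on 2k − 2 degrees of freedom the requirement is 21.7, so 22 clusters per group and 22·2·6 = 264 patients.
- 264/0.75 = 352, and 352/44 = 8 per cluster.

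The stated sample size therefore reproduces, and it includes a design effect of 1.25.

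**Effect of omitting clusters from the economic model.** With m patients per cluster:
- true variance / OLS variance = DE = 1 + (m − 1)·ICC
- shortfall of the standard error = 1 − 1/√DE
- actual type I error of a nominal 5% test = 2·(1 − Φ(1.96/√DE))

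For example, with m = 6 and ICC 0.05, 1.96/√1.25 = 1.753, which gives 8.0%.

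| ICC (assumed) | m | DE | SE too small by | Actual type I error |
|---|---|---|---|---|
| 0.01 | 6 | 1.05 | 2.4% | 5.6% |
| 0.01 | 8 | 1.07 | 3.3% | 5.8% |
| 0.02 | 6 | 1.10 | 4.7% | 6.2% |
| 0.02 | 8 | 1.14 | 6.3% | 6.6% |
| 0.05 | 6 | 1.25 | 10.6% | 8.0% |
| 0.05 | 8 | 1.35 | 13.9% | 9.2% |
| 0.10 | 6 | 1.50 | 18.4% | 11.0% |
| 0.10 | 8 | 1.70 | 23.3% | 13.3% |

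The planned analysed size is m = 6; m = 8 applies if nobody is lost.

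**Check by simulation.** 20,000 trials were simulated with 22 clusters per arm, normal outcomes, equal cluster sizes and no covariates. At ICC 0.05, OLS rejected a true null in 7.8% (m = 6) and 9.1% (m = 8) of trials. A t-test on cluster means of the same data rejected in 4.9% and 5.1%.

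**Probability of cost-effectiveness.** Assume approximately normal net benefit and a simulation whose spread is the OLS standard error. A reported probability P then becomes Φ(Φ⁻¹(P)/√DE). At DE 1.25, reported values of 0.80, 0.90 and 0.95 become 0.77, 0.87 and 0.93. At DE 1.05 they become 0.79, 0.89 and 0.95.

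**The case against.** The strongest reply is that OLS names an estimator of the coefficients and not a variance. OLS with cluster-robust standard errors would fit the wording, the equation is introduced as an example, and a journal article condenses. That reading is possible, but nothing in the text supports it. The section gives equation, covariates, hypothesis and estimator, so this is a stated model that does not match the design rather than a detail left to the SAP.

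Several further objections stand and limit the point:

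- The ICC of 0.05 belongs to the DBI responder endpoint. A reader might infer that the economic tests run at 8% or 9% by the plan's own figures. The protocol does not support that, because it gives no ICC for these outcomes. Near zero the effect is small.
- The effect on the probability of cost-effectiveness is modest over the range shown. It also depends on how the simulation draws its trajectories, and the text does not say which nuisance parameters it uses.
- A reader might infer that the estimated utility and cost differences are themselves biased. They are not biased by ignoring clusters; the uncertainty is what is wrong.
- It is tempting to add that leaving out study center and the T0 value makes the model wrong. A change-score comparison is valid under randomization, and those omissions tend to widen intervals, not narrow them. For falls, Table 10 lists no T0 measurement to adjust for.

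**Conclusion.** The point holds as a mismatch between the written economic model and the cluster-randomized design. Fitted as written, with ordinary OLS standard errors, the tests of δ = 0 are too liberal and the intervals too narrow whenever the ICC is positive. Over an assumed ICC of 0.01 to 0.10 and 6 to 8 patients per cluster, actual type I error runs from 5.6% to 13.3%. At 0.05, standard errors are 11% to 14% too small. The understatement reaches the ICER distribution to the extent that the simulation draws on those standard errors. The primary endpoint analysis is not affected. This should be fixed before analysis, since the implementation recommendation rests on these models, but it does not threaten the trial's main result.

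**What to change.** 1. Fit the utility and cost models with a random intercept per cluster, or keep OLS and state that standard errors are cluster-robust with a small-sample correction for 44 clusters.
2. Generate the ICER distribution from these cluster-adjusted parameters, keeping the correlation between cost and utility. A bootstrap that resamples whole clusters and keeps each patient's cost and utility together is an equally acceptable alternative. The planned Monte Carlo step need not be abandoned.
3. Optional, for precision only: add study center, and the T0 value of the outcome where one is measured.

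The cost is analysis wording and code, with no new data. The intervals widen by a factor of √DE, apart from the small-sample correction. At an ICC of 0.05 that is √1.25 = 1.12 to √1.35 = 1.16, so 12% to 16%; at 0.01 it is √1.05 = 1.02 to √1.07 = 1.03, so 2% to 3%.

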### Health economic evaluation

#### Aims and objectives

The aim of the health economic evaluation is to provide evidence to inform decisions about the potential wider implementation of the intervention. While the ultimate decision is a political one, health economic analysis offers robust scientific insights to support informed policymaking.

Standard criteria for health economic evaluations will be assessed. To justify implementation into routine care, the intervention should meet at least one of the following conditions:

The PARTNER intervention reduces healthcare costs for statutory health insurance (SHI) without negatively impacting patients’ quality of life.The PARTNER intervention improves patients’ quality of life without increasing healthcare costs.The PARTNER intervention enhances quality of life, with associated healthcare cost increases deemed acceptable within cost-effectiveness thresholds.

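### The health-economic steps gate the cost analysis and the ICER on tests of zero difference, so a significant gain on one axis and a non-significant result on the other could be taken as dominance

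*Protocol article*

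**What the plan says.** The aims of the health economic evaluation list three conditions and state that, to justify roll-out, "the intervention should meet at least one of the following conditions". The first is that the intervention "reduces healthcare costs for statutory health insurance (SHI) without negatively impacting" patients' quality of life. The second is that it improves "quality of life without increasing healthcare costs". The third accepts a cost increase within cost-effectiveness thresholds.

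The statistical analysis section of that evaluation then sets out three steps.

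- **Utility.** "We check the null hypothesis that the utility differentials are not associated with whether the patients belong to the IG or the CG"; formally, H0: δ = 0. On estimation, "The Greeks are parameters estimated based on the data via ordinary least squares". The only interpretation given is of rejection: "If the null hypothesis of interest can be rejected, the intervention is associated with different utilities than the standard treatment".
- **Cost.** "If the intervention does not lead to a deterioration in health utility, cost analysis will estimate cost differentials" between the arms, "using an approach similar to that applied for the utility dimensions".
- **Cost-effectiveness.** An ICER, with 10,000 Monte Carlo simulations, follows if the first two steps leave no clear dominance of either alternative.

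The next paragraph of the section announces ICERs for all five utility dimensions. It says the implementation recommendation will rest mainly on the EQ-5D index cost-effectiveness analysis.

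**The concern.** Conditions 1 and 2 each have two halves. One is a gain (lower costs, or better quality of life). The other is a claim of absence (quality of life not harmed, or costs not raised). A test of zero difference can support the gain half. It cannot support the absence half, because non-rejection is compatible with a relevant loss or rise whenever the interval is wide. Yet it is the only test on the page, and both the move to the cost step and the finding of dominance depend on the outcome of such tests.

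The exposure is specific. Suppose costs fall significantly while the EQ-5D difference is non-significant with an interval that includes a relevant loss, or the mirror image. Only one condition has to be met, so this pattern could be declared dominance. On the gating sentence the analysis would stop there, before the one step that carries the uncertainty of both axes. The gate before the cost step has the same weakness: whether costs are analysed at all hangs on a test that was not sized for the purpose.

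**Working it through.** **The plan's own figure first.** The sample size section assumes 10% versus 25% responders, ICC 0.05, 6 evaluable patients per cluster, 80% power and α = 0.05 (two-sided assumed). The design effect is 1 + (6 − 1) × 0.05 = 1.25. With unpooled variance and a t reference on 2(k − 1) degrees of freedom, power is 0.797 at k = 21 clusters per arm and 0.816 at k = 22. So 22 per arm, or 264 patients, is reproduced, and 264 / 0.75 = 352. That calculation is correct, but it covers the primary endpoint only. No size, variance or margin is stated for the health-economic tests.

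**What the same size delivers for a continuous difference.** The article gives no SD for EQ-5D change or for cost, so differences are expressed in SD units of the analysed change. This is an assumption.

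- Per arm: 264 / 2 = 132 evaluable.
- With ICC 0.05: effective n = 132 / 1.25 = 105.6 and SE = √(2 / 105.6) = 0.138 SD. The 95% half-width is 1.96 × 0.138 = 0.27 SD, or 0.28 SD with t on 42 degrees of freedom (critical value 2.018).
- With no clustering (ICC 0, as the printed OLS model would treat it): SE = √(2 / 132) = 0.123 SD and half-width 0.24 SD.

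Chance that a true harm d is not declared significant, using Φ(1.96 − d / SE), or the noncentral t on 42 degrees of freedom in the last column:

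| True harm d | ICC 0, normal | ICC 0.05, normal | ICC 0.05, t on 42 df |
|---|---|---|---|
| 0.10 SD | 87% | 89% | 89% |
| 0.20 SD | 63% | 69% | 71% |
| 0.25 SD | 47% | 56% | 57% |
| 0.30 SD | 32% | 41% | 43% |
| 0.40 SD | 10% | 17% | 19% |

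If nobody drops out (176 per arm, 8 per cluster), the design effect is 1 + 7 × 0.05 = 1.35 and SE = √(2 × 1.35 / 176) = 0.124. A 0.2 SD loss is then still non-significant 64% of the time.

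**Costs.** With an assumed coefficient of variation (CV), a 20% rise is 0.20 / CV in SD units. Under ICC 0.05 and the normal approximation, a true 20% rise is non-significant in 69% (CV 1), 84% (CV 1.5), 89% (CV 2) and 93% (CV 3) of trials.

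**How each pattern runs through the printed sequence.**

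| Utility test | Cost test | Consequence on the gating sentence |
|---|---|---|
| Non-significant | Non-significant | No clear dominance; ICER and simulation follow |
| Non-significant | Significant saving | Could be read as condition 1 and dominance; ICER not reached |
| Significant gain | Non-significant | Could be read as condition 2 and dominance; ICER not reached |

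Only the last two rows are exposed. The percentages above are the error rates of the absence half alone. They are not the probability of a wrong recommendation, which also requires the gain half to be shown.

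**The case against.** Four points can be made for the plan, and much of each stands.

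First, the article never says that a non-significant result means no deterioration or no cost increase. It interprets rejection only. That is correct: the dominance reading is an inference. But no other rule is printed for a step that the procedure cannot do without, and judging by the sign of the point estimate would ignore uncertainty too.

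Second, a reader might infer that noise alone could certify the intervention as harmless or cost-neutral and so meet the criteria. The document does not support this. Conditions 1 and 2 each need a shown gain. If the true effect on the gain axis is zero, a two-sided 5% test shows a gain at most 2.5% of the time, or about 4% if OLS ignores a design effect of 1.25, since P(Z > 1.96 / √1.25) = 0.040. Imprecise data make the absence half easier but the gain half harder, and two null results lead to the ICER.

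Third, a reader might infer that the trial would skip the ICER and recommend roll-out on the tests. The section also promises ICERs for all five utility dimensions, a simulated distribution set against thresholds, and a recommendation resting mainly on the EQ-5D analysis. This weakens the consequence. It does not remove the gating sentence, which says something different, and the two need reconciling.

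Fourth, a numerical margin could sit in a fuller plan that is not shown, so its absence here is not a finding. The printed gating, however, is a stated rule and can be judged as such.

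It is also tempting to point to the EUR 60 per-patient difference in provider payments (180 versus 120) as a cost rise that the test would miss. The article describes those payments as compensation for taking part in the study and builds intervention cost from materials and time multiplied by unit costs, so the example does not carry over.

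**Conclusion.** The point holds in a limited form. The article makes the cost analysis conditional on no deterioration in utility, makes the ICER conditional on no clear dominance, and prints only a zero-difference test to decide either. At 132 evaluable patients per arm that test leaves a 95% half-width of about 0.24 to 0.28 SD and misses a true 0.2 SD loss about 63% to 71% of the time, so non-rejection says little about absence of harm or of extra cost. The range reflects ICC 0 to 0.05 and a normal or t reference; the SD scale and the cost CVs are assumptions. The exposure is confined to a significant gain on one axis paired with a non-significant result on the other. The section also contradicts itself on whether the ICER is always calculated. The primary endpoint and its sample size are unaffected, but the article's own implementation criteria are, so the wording should be changed.

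**What to change.** In the statistical analysis section of the health economic evaluation:

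1. Delete the two conditions. Always estimate the cost difference and the EQ-5D index difference jointly, with cluster-adjusted confidence intervals and the Monte Carlo distribution, whatever the utility test shows. This also settles the conflict with the sentence that promises ICERs for all five dimensions.
2. State that a non-significant difference is not to be read as absence of deterioration or of a cost increase.
3. Declare dominance, or condition 1 or 2, met only when the joint cost-utility distribution or the confidence limits support both halves. Otherwise report the condition as not shown. If confidence limits are used for the absence half, fix the margin before unblinding; the joint distribution needs none.

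The cost is a revised paragraph and slightly more analysis, with no new data or patients. The downside is that results may more often be inconclusive. With 264 evaluable patients, ICC 0.05 and a true difference of zero, the power to exclude a loss of 0.2 SD is 31%, and 83% for 0.4 SD. That reflects what a trial of this size can show.
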